### Variables

2.5

#### Anthropometric measurements

2.5.1

After measuring height and weight, body mass index will be calculated with the following formula:

$$\mathrm{BMI}=\text{weight}(\mathrm{kg})/\text{height}(m^{2})$$

To calculate the percentage of body fat, the subcutaneous fat of the subjects will be measured using a skin thickness gauge in three areas of the abdomen, upper extremities and arms. All skinfold measurements will be performed on the right side of the body in 3 turns with an interval of 20 s to return to the original position. An average of 3 measurements will be recorded and the three-point formula of the American College of Sports Medicine will be used to calculate the percentage of body fat:

$$\begin{array}{c} \mathrm{Fat}\;\text{percent}={\left(0.39278\right)}^{*}(\text{total of three parts})\\ -0.00105^{*}(\text{total of three parts})2\\ +[0.15772^{*}(\mathrm{Age})]-5.18845 \end{array}$$

Anthropometric parameters will be taken by the standardized method of the International Society for the Advancement of Kinanthropometry (ISAK).

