### Participants

2.2

The study will include a total of 80 individuals of both sexes (female, male) with a diagnosis of T2D. Among them, 40 individuals will be required to be on a VitD treatment for at least, 6 months, for reasons recommended by the ECAP working group (including osteoporosis, osteopenia, and VitD deficiency), and the other 40 will not be receiving VitD supplementation.

Subjects will be recruited during usual medical care in a convenience-based by the collaborating physician from the Primary Care Center (CAP) Sant Rafael in Barcelona, Spain.

During the initial visit with the physician at CAP Sant Rafael, participants will be provided with the Patient Information Sheet and the Informed Consent and subsequently will be asked to provide their preferred contact information (phone number or email). This information will be used by the principal investigators from Blanquerna to reach out explaining the study with detailed instructions (explaining the patient information sheet and address any questions they may have). After receiving the information and clarifying any potential concerns, participants will be asked to sign the informed consent.

After enrollment and stratification by VitD treatment status, participants will be randomized within each stratum to exercise intervention or to no exercise. An independent investigator, not involved in recruitment or outcome assessment, will generate the randomization sequence using a computer-based block randomization method within VitD strata. Allocation will be implemented via a secure, web-based central randomization system accessible only after completion of baseline assessments and confirmation of eligibility. This ensures that the four groups (see Table 1) are balanced and clearly defined as: Group 1, Exercise + VitD users; Group 2, Exercise + VitD non-users; Group 3, VitD only (no exercise); and Group 4, Control (no VitD & no exercise).

**Table 1 tab1:** Group allocation of participants with T2D.

Group	VitD treatment status	Exercise intervention	*n*
1	On VitD ≥ 6 months	Exercise program	20
2	No Vit D treatment	Exercise program	20
3	On VitD ≥ 6 months	No exercise	20
4 (Con)	No Vit D treatment	No exercise	20

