### Statistical analysis

2.11

All data will be reported as mean and standard deviation. Data normality and homogeneity of variance will be tested using Shapiro–Wilk and Levens tests, respectively. The primary endpoint (change in HOMA-IR) from baseline to 16 weeks, will be analyzed using ANCOVA with group as the fixed factor, baseline HOMA-IR as covariate, and VitD treatment status included as a stratification variable. Secondary continuous outcomes (glycemic, lipid, inflammatory, anthropometric, dietary, and psychological well-being measures) will also be analyzed with ANCOVA, adjusting for baseline values. Categorical outcomes (e.g., adverse events) will be compared using χ^2^ or Fisher’s exact test. Bonferroni *post hoc* test will be used if there is a significant difference between the groups. Exploratory analyses will test for interaction effects between exercise and VitD status using factorial ANOVA models; these analyses are considered hypothesis-generating due to sample size limitations. In addition, exploratory analyses will be performed to examine potential sex-related differences in primary and secondary outcomes. Sex will also be included as a covariate in the statistical models when appropriate. Statistical power will be calculated by *post hoc* power analysis method by using G Power software.

The results will be analyzed using SPSS (version 22) for Windows. The significant level (*α*) of all statistical analyses will be 0.05.

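### Section 2.5.1 computes percent body fat for both sexes from one equation without a sex term, at skinfold sites that name the arm region twice, and on a curve that flattens as the skinfold sum rises

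*Protocol article*

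**What the plan says.** Protocol article, section 2.5.1 (Anthropometric measurements): skinfolds are taken with a calliper in "three areas of the abdomen, upper extremities and arms", on the right side, as the average of three readings. Then "the three-point formula of the American College of Sports Medicine will be used to calculate the percentage of body fat". With S for the three-site total, the equation printed is:

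percent fat = 0.39278 × S − 0.00105 × S² + 0.15772 × age − 5.18845

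The 2 after the second term stands on the line in the text at hand. It is read here as a lost exponent and is not counted as an error. No second equation appears. The section closes by naming ISAK as the measurement standard.

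Section 2.2 (Participants) plans for "80 individuals of both sexes (female, male) with a diagnosis of T2D". Section 2.4.2 lists weight, BMI, waist circumference and skinfold thickness as anthropometric secondary endpoints, each as a change. Percent fat is not on that list, although the abstract and the hypotheses speak of body composition. Section 2.11 analyses these outcomes by ANCOVA adjusted for baseline, allows sex as a covariate where appropriate, and adds that "exploratory analyses will be performed to examine potential sex-related differences in primary and secondary outcomes".

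**The concern.** There are three separate weaknesses.

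- **No sex term.** The equation returns the same value for a woman and a man with the same age and sum. A sex comparison of percent fat can then only restate differences in skinfold sum and age. A sex covariate in the model cannot restore information that the outcome never held. The protocol does not say for which population the equation is valid.
- **Sites not identifiable.** Arms are upper extremities. The list could mean two arm folds and one abdominal fold, or one of the terms could be a slip for another region. Two assessors could follow the text and measure different folds. This reaches beyond percent fat, because skinfold thickness is itself a listed endpoint.
- **Unequal scaling of change.** A quadratic with a negative second term gives less credit for the same loss when the starting sum is larger. Unlike a constant offset, this does not cancel in a change from baseline.

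At stake are the interpretation of the body-composition results and the reproducibility of one secondary endpoint.

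**Working it through.** **Inputs.** The four coefficients are from section 2.5.1. S is taken in mm, since the section states no unit. The documents give no skinfold values, no split by sex and no validation data, so the values of S below are illustrative. There is no plan figure to reproduce.

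**Sex.** S and age are the only variables in the equation. At equal S and age the difference between a woman and a man is exactly 0, whatever the coefficients.

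**Turning point.** The slope is 0.39278 − 2 × 0.00105 × S = 0.39278 − 0.0021 × S. It is zero at S = 0.39278 / 0.0021 = 187.0 mm. At age 60 the largest percent fat the equation can return is 0.39278 × 187.04 − 0.00105 × 187.04² + 0.15772 × 60 − 5.18845 = 41.0.

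**Credit for a 10 mm loss.** Age and intercept drop out:

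F(S) − F(S − 10) = 3.9278 − 0.00105 × (20S − 100) = 4.0328 − 0.021 × S

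| Starting sum (mm) | Slope (points per mm) | Fall in percent fat for a 10 mm loss |
|---|---|---|
| 60 | 0.267 | 2.77 |
| 100 | 0.183 | 1.93 |
| 120 | 0.141 | 1.51 |
| 150 | 0.078 | 0.88 |
| 165 | 0.046 | 0.57 |
| 180 | 0.015 | 0.25 |
| 200 | −0.027 | −0.17 (a rise) |

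The same loss counts 2.77 / 1.51 = 1.8 times as much from 60 mm as from 120 mm. At 165 mm the slope is 14% of its value at 30 mm (0.0463 / 0.3298), and at 180 mm it is 4.5%. Near-flatness therefore needs a sum of about 165 mm, or 165 / 3 = 55 mm per site on average. At 90 to 120 mm the slope is reduced (0.204 to 0.141) but not flat.

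**Sites.** If the choice of fold alone moved the sum from 60 to 50 mm, percent fat would move by 2.77 points with no change in the patient. The 10 mm is an illustration; the documents do not allow the real size to be estimated.

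**What cancels.** An additive sex offset is the same at baseline and at week 16, so it contributes 0 to the change. The age term adds 0.15772 × 16/52 = 0.05 points over the study, in every arm alike.

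**The case against.** The strongest reply is that little here touches the comparisons the trial will make. The endpoints are changes, exercise is randomised within VitD strata, baseline is a covariate and sex may be one. A constant offset between the sexes disappears. If exercise has no effect on skinfolds, both exercise arms of a stratum have the same expected distribution of sums, so the curvature cannot by itself create a difference. Percent fat is not among the endpoints in section 2.4.2, whereas raw skinfold thickness is. All of this stands, and it is why the severity is low. A sex-dependent slope would not cancel, but the documents give no means of sizing one.

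It can also be said that a condensed article leaves site detail to the full protocol, and that ISAK fixes the method. The first part does not help: the article does state the sites, in a form that cannot be followed. The second is only half an answer, because ISAK is cited for technique and the sentence does not say which three folds enter the sum.

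A reader might go further and infer that percent fat is biased in women by a definite amount, or that the planned sex comparison is an artefact. The documents do not support this. They do not say in which sex the equation was derived and offer no reference values, so neither direction nor size of a bias can be shown. The sex analyses in section 2.11 also concern the primary and secondary outcomes, which are changes and mostly do not involve this equation.

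A reader might likewise infer that change is unmeasurable in heavier patients. That holds only if sums reach about 165 mm, which is not reported.

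**Conclusion.** The point holds as a low-severity defect of measurement definition. Two parts follow from the text alone: one equation that cannot distinguish the sexes is applied to both without a stated basis, and the three sites are not identifiable as printed. The third follows by arithmetic from the printed coefficients, with the 2 read as an exponent and S in mm: equal losses score unequally, 2.77 points from 60 mm against 0.88 from 150 mm.

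The effect on between-arm change is expected to be small, for the reasons of cancellation and randomisation given above, and the primary endpoint (HOMA-IR) is unaffected. The site ambiguity deserves most attention, since it also affects a listed endpoint and cannot be repaired once baseline folds have been taken.

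**What to change.** Before any baseline measurement, amend section 2.5.1 to:

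1. Name three distinct ISAK sites that match the equation used, and require the same sites at baseline and at the end of the study.
2. Use sex-appropriate equations, or state and justify the population in which the printed one is valid.
3. Compare arms on the change in the raw skinfold sum, which fits the skinfold-thickness entry in section 2.4.2, and report percent fat descriptively only.

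The third step is what removes the unequal scaling. Replacing one quadratic equation by another would leave a turning point in place.

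The cost is a change of wording, plus possibly different fold sites for women and men if the equations chosen require them. In that case the raw sum should be compared between arms within sex or with sex in the model. The calliper and the number of folds stay the same.

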#### Food consumption and adherence to the Mediterranean diet

2.5.2

Nutritional questionnaires will be provided in person during the first visit at the participating pharmacies, right after recruitment. Adherence to the Mediterranean dietary pattern will be determined using the Mediterranean Diet Adherence Screener (MEDAS) developed in the PREDIMED study. MEDAS is a questionnaire consisting of 14 questions. Values of 0 or 1 are assigned to each item, the maximum adherence to the Mediterranean Diet is indicated by a 14-point score (26). A validated food frequency questionnaire (FFQ) with 137 items plus specific questions for patterns of alcohol consumption and vitamin/minerals supplements will also be administered (adapted from the Willett questionnaire and validated in Spain) (27).

The inclusion of these dietary assessments aims to provide valuable insights into the eating habits of the selected population before the study. Based on the participant’s diet, during the study we will reinforce the recommendations of the Spanish Society for Diabetes. Nutritional education programs based on the previously mentioned recommendations will be provided to participants, where adaptations can be designed to participant particular needs (age, gender, activity, DM treatment, etc.) (28). Moreover, the gathered data will also serve to normalize the overall diet of all participants during the study.

In addition to the questionnaires, dietary intake and adherence will be briefly reviewed during the follow-up via monthly telephone interviews and pharmacy visits to check consistency of responses and reinforce adherence. Participants may also keep short dietary notes or logs if feasible.

#### Activity degree and psychological well-being

2.5.3

Activity degree and psychological well-being questionnaires will be provided during the first visit at the participating pharmacies, right after recruitment. To evaluate the degree of activity, the questionnaire validated in Catalan, Qüestionari Internacional d’Activitat Física (29), will be administered to measure the physical activity, which through an interview assessing different items will allow to obtain the usual physical activity, being able to classify individuals in sedentary, moderate sedentary or active lifestyles and will serve to evaluate overall physical activity degree for further comparisons and analysis.

The psychological subjective well-being will be measured through the Psychological Well-being Index (IBP; Índex de Benestar Psicològic), which refers to happiness or well-being. Therefore, greater subjective perception of well-being will give higher scores (30). This comprehensive assessment will be conducted both before and after the intervention, allowing for a comparative analysis of changes in psychological well-being over the course of the study.

#### Blood sampling and analysis

2.5.4

A total of 2 blood samples will be obtained during the study. The analyses will be conducted at the following times:

After the first visit, at baseline, and before the intervention (complete blood analysis, including VitD).At the end of study, at month 4, after the exercise intervention (complete blood analysis, including VitD).

All subjects will go in the morning at their respective Primary Care Centers after 12 h of fasting. Blood sampling will be performed at the corresponding CAP. Blood samples will be analyzed by the Servei de Bioquímica Clínica (Hospital Universitari Vall d’Hebron).

The blood parameters to be determined are the following:

Vit D (cholecalciferol)InsulinGlucoseGlycosylated hemoglobinTotal CholesterolLDL cholesterolHDL cholesterolTriglyceridesHepatic profileMicroalbuminuriaHemogramRenal functionC reactive proteinErythrocyte sedimentation rateFerritin

HOMA-IR index will also be calculated as previously described (31) by using formula (HOMA-IR = fasting glucose in mmol/l*fasting insulin in μU/ml/22.5) to determine insulin resistance. HOMA-B index to quantify the pancreatic beta cell function using formula (HOMA-B360 x fasting insulin (μU/mL)/(fasting glucose (mg/dL)−63)) will be determined.

#### Pharmacist role

2.5.5

The role of the pharmacist in patient follow-up will be evaluated as an exploratory process endpoint. This includes documenting completion of scheduled follow-up visits, administration of dietary and psychological questionnaires, monitoring of medication adherence, and reporting adverse events.

Pharmacists involved in the study will be licensed professionals, also PhD holders or doctoral candidates, trained by the study team in protocol procedures, participant education, and safety monitoring.

### Familiarization with resistance training to measure one maximum repetition (1RM)

2.6

During an initial familiarization session, the subjects will be instructed how to properly perform the resistance training program and will receive detailed safety recommendations. The trainer will first demonstrate the movements, after which participants will practice them without weights. Real-time feedback will be provided to ensure correct technique and reduce the risk of injury. Maximum strength or one maximum repetition (1RM) in all movements will not be directly tested, but will be indirectly estimated online using the validated Brzycki equation (32):

1RM=lifted weight(kg)/1.0278−(frequencies×0.0287)

Training intensities during the intervention will be prescribed as a percentage of the estimated 1RM and will be further adjusted according to participants’ perceived exertion and feedback to ensure both safety and adherence.

### Sarcoplasm-stimulating training program

2.7

A sarcoplasm-stimulating training program will be used as the primary intervention model. This program combines resistance and aerobic components with short rest intervals between sets, designed to increase metabolic stress and enhance both muscular endurance and insulin sensitivity. Such adaptations are particularly relevant in patients with T2D, where resistance training has been shown to improve glycemic control, body composition, and inflammatory status (6, 8, 20). In addition, this training format can be implemented safely in an online, home-based setting without the need for specialized equipment, making it feasible and scalable in real-world primary care contexts.

This is a home training program where sessions are conducted online via corporate Teams from Blanquerna, Universitat Ramon Llull. Participants will not require any additional material, as the physical activity program has been specifically designed to be performed without equipment. Participants will receive in person by the investigator and personal trainer, the link and access codes during their initial visit to the community pharmacy.

The program consists of one familiarization week followed by three progressive 5-week phases (weeks 1–15), each with gradually increasing intensity and reduced rest intervals (see Table 2). In Week 1 after familiarization, participants will perform 4 sets of 8 repetitions at 60% of 1RM, with 20 s of rest between sets. In Week 2, the same format will be maintained with slightly higher intensity (65% 1RM). In Week 3, each movement will be performed in 5 sets of 6 repetitions at 75% of 1RM, with 20 s of rest. In Week 4, the number of sets and repetitions will be maintained but the intensity of training will increase to 80% of 1 RM. In Week 5, considered a tapering phase, participants will perform 5 sets with 4 repetitions at 70% of 1RM, again with 20 s of rest between each set. This 5-week progression will be repeated and advanced through Weeks 6–10 and Weeks 11–15.

**Table 2 tab2:** Distribution of the sarcoplasm-stimulating training program (weeks 1–15).

Phase	Week	Sets × repetitions	Rest interval (seconds)	Intensity (% 1RM)
Familiarization	–	Technique practice, no external load	–	–
Phase 1	1	4 × 8 reps	20	60%
	2	4 × 8 reps	20	65%
	3	5 × 6 reps	20	75%
	4	5 × 6 reps	20	80%
	5 (taper)	5 × 4 reps	20	70%
Phase 2	6	4 × 8 reps	20	60%
	7	4 × 8 reps	20	65%
	8	5 × 6 reps	20	75%
	9	5 × 6 reps	20	80%
	10 (taper)	5 × 4 reps	20	70%
Phase 3	11	4 × 8 reps	20	60%
	12	4 × 8 reps	20	65%
	13	5 × 6 reps	20	75%
	14	5 × 6 reps	20	80%
	15 (taper)	5 × 4 reps	20	70%

1RM: maximum repetition.

All exercises are designed as a combination of aerobic and resistance training, following the principle of sarcoplasm stimulation, which emphasizes reduced rest intervals to enhance metabolic stress and muscular adaptation (6, 8, 20).

The total duration of 16 weeks, including one familiarization week, was selected based on previous studies reporting significant metabolic and functional adaptations within 12–16 weeks of combined aerobic and resistance training in patients with T2D (21, 24). This time frame provides sufficient physiological stimulus to detect improvements in insulin resistance, strength, and body composition while maintaining participant adherence in a home-based program.

To enhance adherence and ensure correct execution of the home-based, online exercise program, several strategies will be implemented. First, participants will attend the initial familiarization session, during which individualized feedback will be provided to ensure proper technique and understanding of the training protocol. Second, all exercise sessions will be delivered as life online, supervised in real time by the personal trainer who will monitor attendance and performance. Third, participants will attend monthly follow-up visits at the collaborating pharmacies, where pharmacist (in collaboration with the personal trainer) will review adherence, discuss potential difficulties and provide reinforcement of study instructions. Fourth, monthly telephone interviews will be conducted by the study team to assess adherence, identify any adverse events, and resolve technical issues related to the online delivery of the program. In addition, participants will be asked to complete self-reported exercise logs documenting session completion, perceived effort and any difficulties encountered. These logs will be collected and reviewed monthly by the personal trainer to ensure compliance and to provide tailored feedback when necessary.

Personal trainers involved in the study will hold accredited university degrees in Sport Sciences and will be either PhD holders or currently enrolled in a doctoral program, with prior experience prescribing and supervising resistance and aerobic exercise in clinical populations.

### Current medication

2.8

During the first visit at the CAP, participating physicians will collect information regarding the current medication of diabetic patients. This information will serve as baseline data and aid in the interpretation of outcomes, adjustment in statistical analyses, and support a more individualized approach to patient care. Additionally, the data can be utilized to identify common treatment patterns, assess adherence to prescribed therapies, and explore the relationship between medication regimens and patient outcomes.

### Participant visits and follow-up

2.9

A total of 6 visits are expected per each participant. The study includes a first visit at the designated CAP for the explanation of the study, right before the intervention. During this first visit, physicians from CAP Sant Rafael will thoroughly assess participants to confirm their eligibility for the study. During the initial visit, the physicians will provide potential participants with the Patient Information Sheet and the Informed Consent allowing them time to review the documents at home. During this first visit, participants will be asked to provide their preferred contact information (phone number or email), which will be later used to send detailed instructions, the list of participating pharmacies, and to initiate their participation in the study. Blanquerna investigators will explain the study protocol using the patient information sheet and will set a meeting at the community pharmacy. Pharmacies will collaborate solely by providing the space, while all study activities will be conducted by the investigator’s pharmacist from Blanquerna.

Once the patients signed the informed consent, blood samples will be requested by the physicians from CAP Sant Rafael for clinical analysis; this analysis will take place during the second visit at the CAP.

The collaborating community pharmacies from the geographical area of the study can be seen in Table 3.

**Table 3 tab3:** Collaborating pharmacies near CAP Sant Rafael.

Pharmacy	Contact information
[name]	[name]. [contact]
[name]	[name]. [contact]
[name]	[name]. [contact]
[name]	[name]. [contact]
[name]	[name]. [contact]
[name]	[name]. [contact]
[name]	[name]. [contact]
[name]	[name]. [contact]
[name]	[name]. [contact]
[name]	[name]. [contact]
[name]	[name]. [contact]
[name]	[name]. [contact]
[name]	[name]. [contact]
[name]	[name]. [contact]
